## Methods/Design

### Aim and research questions

The primary aim of this study is to test the efficacy of brief behavioral counselling, delivered by allied health professionals, to increase physical activity in people with PAD. Secondary aims are to examine the effect of the counselling on functional capacity, revascularisation rate, clinical events, and resource use; and to perform an economic evaluation of the counselling intervention compared to usual care. This fills an important gap in the literature on PAD clinical management, and will address the following questionscan brief behavioural counselling be delivered by health professionals who are not qualified psychologists, following training?can the brief behavioural counselling be effectively delivered in a variety of different centres by different professionals?is delivery of the brief behavioural counselling in a health care setting effective in achieving sustained physical activity behaviour change?

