### Design and setting

This is a multicentre, prospective, randomised superiority trial with two parallel study groups: a control and an intervention group. The trial will be conducted in four cities across Australia. Study sites will include three specialist vascular management clinics (Townsville, Brisbane, Perth) and a University clinic (Sydney).

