### Sample size calculation

We hypothesise that over a 4-month period the intervention will increase physical activity by ~50 %, evidenced by mean daily step counts of 5000 ± 3400 for those receiving the counselling intervention compared to 3300 ± 2200 for those randomised to the control group. We also hypothesise that these effects will be maintained at 12 and 24 months post intervention. The effect size and outcome results estimated are based on data from a previous trial [54]. We require 62 participants per group (power 90 %, alpha 0.05, within-subject between visit correlation 0.6) to detect the hypothesised increase in physical activity. Allowing for maintenance of this increase over 24 months, and a drop out of up to 40 %, we require 100 participants per group. We therefore will aim to recruit a total of 200 people.

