### Randomisation

Eligible and consenting individuals who complete the baseline assessment will be randomly allocated to the control or intervention group. The allocation sequence will be computer-generated using a random number sequence and allocation will occur in block sizes up to 4 and will be stratified based on ABPI (<0.50, 0.50-0.69, 0.70-0.89, >1.4), study site, and gender. Allocation is concealed by using a central randomisation site, and different project staff for assessment and allocation/intervention delivery. Participants will be blinded to allocation and the investigators’ hypotheses. Intervention staff will conduct both intervention and control participant contacts, and therefore cannot be blinded to allocation. They will be instructed not to disclose the allocation status to either the participants or assessment staff.

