Between group differences in physical activity (primary outcome) and other measures will be analysed using an intention-to-treat approach and repeated measures mixed models. All continuous data will be inspected for normality of distribution visually and statistically, and non-normally distributed data will be mathematically transformed if possible prior to use with parametric statistics. Covariates considered for use in these models include age, gender and any characteristics significantly different between groups at baseline which could potentially confound the variable of interest in each model. Predictors of changes in primary and secondary outcomes will be identified using simple and multiple regression models of relevant baseline characteristics (e.g., BMI and education). The incidence of revascularisation in the intervention and usual care control groups will be compared by chi-square test or logistic regression adjusted for relevant baseline characteristics if needed. Binomial logistic regression will be conducted to identify factors that predict revascularisation. Differences in time to revascularisation will be analysed by Kaplan Meier analysis and log rank test. Given the low risk of the behavior intervention planned in this study it is highly unlikely that the trial would require stopping and thus no interim analysis is planned. Relative effect sizes and 95 % Confidence Intervals for primary and secondary outcomes will be calculated. A *p* value of <0.05 will be accepted as statistically significant, given that all hypotheses to be tested have been formulated *a priori.*

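### Site and ABPI stratify the randomisation, but the stated covariate rule admits them only if imbalanced at baseline, and no described analysis informs the question about centres

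*Protocol article*

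**What the plan says.** Under Randomisation, "allocation will occur in block sizes up to 4 and will be stratified based on ABPI (<0.50, 0.50-0.69, 0.70-0.89, >1.4), study site, and gender". Under Design and setting, "The trial will be conducted in four cities across Australia".

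Under Data management and analyses, "Between group differences in physical activity (primary outcome) and other measures will be analysed using an intention-to-treat approach and repeated measures mixed models". The same section gives the covariate rule: "Covariates considered for use in these models include age, gender and any characteristics significantly different between groups at baseline", the last group limited to those that might confound the variable being modelled. Gender is the only stratification factor named, and it too is only considered, not fixed.

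Under Aim and research questions, one of the three questions the trial sets itself is "can the brief behavioural counselling be effectively delivered in a variety of different centres by different professionals". The analysis section describes no site term, no treatment-by-site term and no site-specific estimate. Its regressions for predictors of change give BMI and education as examples, which are participant characteristics.

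**The concern.** Stratified blocks exist to balance site and ABPI between the groups. A rule that admits a covariate because it is imbalanced will therefore tend to leave out the very factors the design has controlled. If those factors predict the outcome, the randomisation has removed much of their variation from the treatment contrast while the model still counts it as error. The standard error is then overstated and some precision is thrown away.

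The centres question is a separate matter. A pooled effect carried by one centre would look the same, in the analyses described, as an effect seen at all four. The Discussion rests wider applicability on the range of professionals and settings, so some display of results by site would be expected.

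**Working it through.** **Inputs from the article.** Means 5000 (SD 3400) for intervention and, in its words, "compared to 3300 ± 2200 for those randomised to the control group"; difference 1700 steps/day; power 90 %, alpha 0.05 (taken as two-sided); correlation 0.6; 62 per group; drop-out up to 40 %; 100 per group randomised. Strata: 4 sites × 4 ABPI bands × 2 genders = 32, so 200/32 ≈ 6 participants each.

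**Input not in the article.** R², the share of outcome variance explained by site and ABPI. I take 0.05 to 0.20 as the working range.

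**Step 1: the plan's own figure.** SD = √((3400² + 2200²)/2) = 2864, so SD² = 8.2 million. n = 2 × 8.2 million × (1.960 + 1.282)²/1700² = 59.6, which rounds up to 60 per group (61 with a Welch t calculation). This is within two of the stated 62, but only if the 0.6 correlation is left unused; an analysis adjusted for baseline would need 39–40. With 40 % drop-out, 100 per group leaves 60 completers.

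**Step 2: upper bound, assuming perfect balance and no baseline term.** The standard error without the strata is √(2 × 8.2 million/60) = 523 steps/day. With them it is 523 × √(1 − R²). The type I error of the unadjusted test is 2(1 − Φ(1.96/√(1 − R²))).

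**Step 3: a more realistic check.** Perfect balance does not hold with small strata, incomplete blocks and 40 % drop-out. I simulated 5000 trials per R²: 200 participants, 32 strata, blocks of 4, random drop-out of 40 %, gender in every model, R² split equally between site and ABPI. Assumed shares were 35/30/20/15 % for sites and 10/30/50/10 % for ABPI bands. A single follow-up was analysed by linear regression, as a simplification of the repeated-measures model.

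| R² | SE with strata (Step 2) | Excess if omitted | Type I error (Step 2) | Simulated model SE vs true SE, strata omitted | Excess | Simulated type I error |
|---|---|---|---|---|---|---|
| 0.05 | 510 | 2.6 % | 0.044 | 525 vs 519 | 1.2 % | 0.044 |
| 0.10 | 496 | 5.4 % | 0.039 | 523 vs 512 | 2.1 % | 0.043 |
| 0.20 | 468 | 11.8 % | 0.028 | 524 vs 501 | 4.6 % | 0.040 |

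Simulation error is about 0.003 on the type I error (√(0.05 × 0.95/5000)) and about 1 % on the true SE (1/√(2 × 5000)), so the smallest excess is barely distinguishable from zero.

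With baseline steps in the model (correlation 0.6) and site and ABPI still omitted, the model SE is 420–421 against a true SE of 416–423, and the type I error is 0.045–0.050, for R² from 0.05 to 0.30.

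**Step 4: power.** From Step 2, with 60 completers per group and no baseline term, power is 90.2 % without site and ABPI. With them it is 91.6 %, 92.9 % or 95.3 % at R² 0.05, 0.10 or 0.20. If R² is 0, adjustment gains nothing: the simulated model SE goes from 525 to 532, about 1 % worse.

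**Step 5: what site-specific estimates can show.** Assume equal sites: 50 randomised, 25 per arm, 15 completers per arm.

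- One site, unadjusted: SE = √(2 × 8.2 million/15) = 1046; 95 % half-width 1.96 × 1046 ≈ 2050. Power for 1700 is about 37 %.
- One site, baseline-adjusted: SE = 1046 × √(1 − 0.6²) ≈ 836; half-width ≈ 1640. Power is about 53 %.
- Difference between two sites, baseline-adjusted: SE = 836 × √2 ≈ 1180; half-width ≈ 2320, more than the whole hypothesised effect of 1700.

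**The case against.** The strongest reply is that the covariate list is open: it says what is considered and what is included among it, and final model terms may stand in an analysis plan that is not shown. That is right as far as it goes. A reader might infer that the models will certainly contain neither site nor ABPI; the article does not say so. What stands is that the one selection criterion it does state works against these two factors.

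A reader might also infer that standard errors are certainly too large, by 5–12 %, with a true type I error as low as 2.8 %. The documents do not support that. It needs site or ABPI to be prognostic, perfect balance among completers and no baseline-steps term. Baseline steps are measured, and a repeated-measures model may well use them. Counting gender in the R² would inflate the figure further, since gender is already a named covariate.

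On centres, the design itself goes part of the way: four cities, professionals who are not psychologists, an 80 % competency threshold and fidelity checks on recorded sessions. The article does not state equal effects across sites as a hypothesis. This is fair, and it means no formal test of interaction is owed. Those features show that delivery was attempted and checked. They do not show whether it was effective at each centre.

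Finally, fixed effects for every stratum could be impractical where revascularisations are few. I accept this and limit the fix to the continuous outcomes.

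**Conclusion.** The point holds as a poorly chosen covariate rule with a small effect. Site and ABPI are balanced by design and then subjected to a screen that balance makes them unlikely to pass. If they predict steps, the reported standard error is too large by roughly 1–5 %, and the type I error is about 0.044–0.040, for an assumed R² of 0.05–0.20 and no baseline-steps term. With baseline steps modelled the effect is close to nil. The error is in the conservative direction: false positives are not inflated, and the planned 90 % power is met with or without these terms under the article's own assumptions.

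The gap on the centres question does not depend on R²: no analysis in the article matches it. A reader might expect by-site results to expose gross inconsistency. Step 5 shows that they could not do so reliably, because a full effect at one site and none at another would usually not be separable. Site sizes may also be unequal, since starts were staggered and Perth was still pending when the article was submitted; smaller sites would be less precise still.

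**What to change.** Replace selection by baseline significance with a pre-specified set: site, ABPI stratum and gender as fixed effects in the repeated-measures models for the continuous outcomes. Collapse ABPI bands where they are sparse.

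Before ABPI stratum can be used as a model term, the bands need reconciling with the inclusion criteria. The bands have no category for 0.90 to 1.40, while the and/or wording under Participants can admit patients in that range on symptoms or absent pulses.

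Report site-specific 4-month effects with 95 % confidence intervals, labelled in advance as descriptive and as informing the centres question. State that they are too imprecise to establish or exclude differences between centres.

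The cost is wording and a few degrees of freedom: six for site and ABPI with four levels each, or about 1 % on the standard error if neither factor is prognostic. No new data are needed.

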### Assessment

Assessments will be conducted at baseline and 4, 12 and 24 months by staff blinded to participant allocation. Each assessment time point will comprise two facility-based visits approximately one week apart, the first for 90 min, and the second for 60 min. At visit 1 (90 min) participants will provide a blood sample and complete physical activity and health-related quality of life questionnaires. The Short Physical Performance Battery (SPPB) and 6-min walk test (6MWT) will be undertaken. An assessment of ABPI will be performed. Smoking status, medical and surgical history, anthropometry, resting heart rate, brachial blood pressure and ambulatory ability will also be assessed. At the end of visit 1, participants will be fitted with an activPAL3™ accelerometer, which will be worn for seven consecutive days. At visit 2 (60 min), participants will return the activPAL3™ accelerometer, and complete additional physical activity and health related quality of life questionnaires. At baseline only, the six minute walk test is repeated at visit 2. Participants will be given the written PAD information sheet at the end of visit 2. Assessments at 4, 12 and 24 months will also include the recording of any study defined clinical events since the previous visit.

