### Primary outcome measures

The primary outcome measure will be daily physical activity level or walking (i.e. steps per day). This will be assessed using an activPAL3™ accelerometer (PAL Technologies Ltd, Glasgow, United Kingdom) which is a triaxial accelerometer that assesses body position (i.e. sitting/lying and standing) and walking activity from accelerometer recordings at a sampling rate of 20 Hz and sensitivity of ± 2 g [57, 58]. The activPAL3™ unit will be wrapped in a nitrile sleeve, wrapped in waterproof dressing and attached to the right thigh of each participant using adhesive waterproof dressings (mid-line; 1/3 of the distance from the inguinal fold to the top of the patella). Recordings will commence at 06:00 on the following morning and continue for seven full days whereupon the activPAL3™ unit will be removed, returned to the investigators and the recording uploaded for analysis. Data are checked to ensure data has been recorded for the period, and if not, participants are asked to redo the assessment. The activPAL3™ has been reported to be reliable and valid in the assessment of walking, body posture, and sedentary behavior during free-living activity [57, 59, 60] and when used with older adults [61] and patients with IC [62].

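### Baseline significance tests help decide which covariates enter the models, no covariate is fixed, and adjustment for baseline steps/day is not secured

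*Protocol article*

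**What the plan says.** The primary outcome is fixed as steps per day: "The primary outcome measure will be daily physical activity level or walking (i.e. steps per day"). On timing, the Assessment section states: "Assessments will be conducted at baseline and 4, 12 and 24 months by staff blinded to participant allocation". Group differences in this and the other measures "will be analysed using an intention-to-treat approach and repeated measures mixed models".

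The next rule on the models concerns covariates: "Covariates considered for use in these models include age, gender and any characteristics significantly different between groups at baseline which could potentially confound" the outcome being modelled. Three features matter.

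- Age and gender are candidates, not commitments.
- Any other characteristic becomes a candidate through a significant baseline test, subject to a loose condition that it might confound.
- Baseline steps/day is not named, and the section does not say whether the baseline visit is one of the repeated outcomes.

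The Sample size calculation section does give the correlation between visits as an input: "We require 62 participants per group (power 90 %, alpha 0.05, within-subject between visit correlation 0.6"). The Randomisation section stratifies on ABPI category, study site and gender. Of these, only gender is named among the covariates.

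**The concern.** After concealed random allocation, any baseline difference between the groups is due to chance. A significance test on it says nothing about whether the variable should be adjusted for. Adjustment earns its place through the strength of the variable's relation to the outcome, which can be judged before the data are seen. A rule based on baseline tests can bring in a weak predictor that happens to differ and leave out a strong one that happens to balance. The adjustment set then depends on the data and can differ from outcome to outcome for no prognostic reason.

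The protocol itself points to one strong predictor. If steps/day correlate at 0.6 between visits, the baseline count explains 0.6² = 36 % of the variance at follow-up. Under the covariate rule, baseline steps would qualify through a significant difference in only about 5 % of trials. At stake are the precision of the primary estimate and the claim that the analysis was set in advance. The same section relies on that claim when it accepts p < 0.05 because the hypotheses were formulated beforehand.

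**Working it through.** **Inputs.** From Sample size calculation: "mean daily step counts of 5000 ± 3400 for those receiving the counselling intervention compared to 3300 ± 2200 for those randomised to the control group"; 90 % power; alpha 0.05; correlation r = 0.6; 62 per group; and "a drop out of up to 40 %, we require 100 participants per group". Assumptions: alpha is two-sided, and the SD is the same at baseline and at follow-up (no baseline SD is given).

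**Step 1: the plan's own figure.**
- Difference: 5000 − 3300 = 1700 steps/day.
- Root-mean-square SD: √[(3400² + 2200²)/2] = √8,200,000 = 2863.6. Standardised effect: 1700/2863.6 = 0.594.
- n per group = 2(1.960 + 1.282)² × (2863.6/1700)² ≈ 59.6, so 60. The t-based version gives 61.
- The stated 62 is therefore reproduced to within 2 as a plain two-sample comparison that ignores r.
- Using r does not reproduce it. Change from baseline multiplies the variance by 2(1 − 0.6) = 0.80 and gives 48. Baseline adjustment multiplies it by 1 − 0.6² = 0.64 and gives 39.

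**Step 2: what each use of baseline delivers.** With 40 % dropout from 100, 60 per group complete. The unadjusted standard error is 2863.6 × √(2/60) = 522.8. Power comes from the noncentral t distribution.

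| Use of baseline | Relative variance | SE (steps/day) | 1700/SE | Power |
|---|---|---|---|---|
| None | 1.00 | 522.8 | 3.25 | 89.7 % |
| Change from baseline (free baseline means) | 0.80 | 467.6 | 3.64 | 95.0 % |
| Baseline-adjusted | 0.64 | 418.3 | 4.06 | 98.1 % |

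Relative to the adjusted analysis, the standard error is √(1.00/0.64) = 1.25 times as large with no baseline and √(0.80/0.64) = 1.118 times as large for change. By the normal approximation, the difference detectable with 90 % power is about 1695, 1516 and 1356 steps/day in the three rows.

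**Step 3: the rule taken literally.** In 20,000 simulated trials (60 per group, common SD 2863.6, r = 0.6, one follow-up visit), baseline entered as a covariate only when its own test gave p < 0.05.

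| Strategy | Power at 1700 | Type I error |
|---|---|---|
| Never adjust | 89.5 % | 5.1 % |
| Adjust only if the baseline test is significant | 90.8 % | 4.0 % |
| Always adjust | 98.0 % | 5.1 % |

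The rule recovers almost none of the gain, and its type I error is below the nominal level.

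**Step 4: how often chance would add something.** If k independent characteristics are tested at 0.05 (k is an assumption), at least one is significant with probability 1 − 0.95^k. That is 40 % for k = 10 and 64 % for k = 20.

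**The case against.** The strongest reply is that a repeated measures mixed model may already use baseline. Participants are measured at baseline and three later visits. If the baseline visit is one of the repeated outcomes, the group-by-time contrast uses the correlation: in part if the baseline means are free, and almost fully if they are constrained equal. A reader might infer that the plan discards the gain from r = 0.6. The text does not support that, because it leaves the role of the baseline visit open. A journal article may also leave that detail to the analysis plan. The fair statement is that the gain is not secured.

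A reader might also infer that the trial is underpowered. It is not: the 62 per group does not depend on the correlation, and 60 completers keep about 90 % power even if baseline is ignored.

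A third tempting inference is an inflated type I error. For the literal rule the simulation shows the opposite, about 4 %. Because covariates are only considered, there is room for discretion. Always reporting the smaller of the adjusted and unadjusted p-values would give about 8 %, but nothing in the protocol says or suggests that this will be done.

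Finally, the rule does carry a relevance condition, since a characteristic must be able to confound. That narrows the candidates. It does not cure the fault, because the significance test still has to be passed and the condition is a matter of judgement. Using different covariates for different outcomes is also not wrong in itself.

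The selection rule remains. It is stated in the text, so it is not a detail left to the analysis plan, and a plan written to follow it would inherit the fault.

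**Conclusion.** The point holds as a criticism of the covariate rule. Chance imbalance helps decide the adjustment set, nothing is fixed, and baseline steps/day is not guaranteed a place in the primary model. The cost is available precision: power of 89.7 % to 95.0 % where 98.1 % could be had from the same participants, or a standard error 25 % or 12 % larger than necessary. No bias, no inflation of the type I error and no shortfall from the planned 90 % has been shown.

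The sizes rest on r = 0.6 applying between baseline and follow-up, equal SDs at the two times, a two-sided 5 % level and 60 completers per group. The figures of about 91 % power and 4 % type I error apply only to a follow-up comparison in which baseline is a conditional covariate. If the mixed model already includes baseline as an outcome, the loss is smaller and may nearly vanish. This should be fixed, but it does not threaten the trial.

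**What to change.** In Data management and analyses, delete the clause that admits characteristics because they differ significantly at baseline. Fix the primary model in advance:

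- outcome: steps/day at 4, 12 and 24 months;
- terms: treatment, visit and treatment-by-visit;
- baseline steps/day, either as a covariate or as an additional outcome with the group means constrained equal;
- the stratification factors (ABPI category, site, gender) and age.

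For every other continuous outcome, use the same structure with that outcome's own baseline value. Any model with further covariates should be labelled a sensitivity analysis.

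The cost is wording in the protocol and analysis plan. All the variables are already collected and the sample size need not change. The edit should be dated before unblinding.

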### Secondary outcome measures

In addition to the primary measures of daily physical activity level and walking (steps/day), other outcome measures from the activPAL3™ will include daily sedentary (sitting/lying) time, number of sit-to-stand transitions, and energy expenditure (total number of kilocalories per day). Other secondary outcome measures using objective assessment will include:Ambulatory ability and lower body functioning: This will be assessed using the 6MWT, and the Short Physical Performance Battery (SPPB) which have previously been used as outcome measures in PAD intervention trials [36, 37]. The 6MWT assesses maximal cardiorespiratory fitness and correlates strongly with physical activity levels among people with PAD, and may therefore reflect walking capacity in everyday life [63]. The SPPB includes three objective tests of lower body function: A hierarchical test of standing balance, a timed 4-m walk and 5-timed repetitive chair stands. The SPPB strongly predicts loss of ability to walk 400 m [40], and is predictive of hospitalisation, nursing home admission and mortality [38, 39, 64]. It is a widely used and valid measure with established test-retest reliability [65].Event-based claudication index (EBCI) which is a measure of the ratio of walking bouts to upright time assessed from accelerometer data. Individuals with PAD have a greater EBCI than age matched controls, which indicates a fragmented stop/start walking pattern [47, 62].Vascular interventions including endovascular and surgical lower limb revascularisations and aneurysm repair.Clinical events including cardiovascular events, amputations, vascular and cardiac surgeries/interventions, musculoskeletal injury, other injuries or illness and death determined from patient reviews and hospital chart reviews, as described elsewhere [66, 67].Circulating pro-thrombotic markers, pro-inflammatory cytokines, lipids and RNA expression of circulating cells will be examined at the completion of the trial using stored blood samples obtained at each visit. EDTA and citrate plasma, serum and total blood collected into Paxgene tubes will be obtained at each assessment time. We have previously established methods to assess vascular biomarkers with good repeatability in our central laboratory [68–74].Measures of cardiovascular function including heart rate, blood pressure and ABPI assessed with standardised protocols as described elsewhere [75].Body composition including waist and hip circumference and body mass index assessed with standardised protocols as described previously [76].

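### Formulating hypotheses in advance does not justify p<0.05 for every test when steps/day is hypothesised at three visits and no primary visit, contrast or testing order is named

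*Protocol article*

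**What the plan says.** The significance rule stands at the end of the statistical paragraph under Data management and analyses: a p "value of <0.05 will be accepted as statistically significant, given that all hypotheses to be tested have been formulated" a priori. It covers every test in that paragraph: the primary outcome, the other measures, the revascularisation comparisons and the regressions that look for predictors.

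The primary outcome is given without a time: "The primary outcome measure will be daily physical activity level or walking (i.e. steps per day"). The Assessment section measures it at baseline and at 4, 12 and 24 months. The analysis is a repeated measures mixed model under intention to treat, with no contrast singled out.

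The Sample size calculation section has hypotheses at all three follow-up visits. The first reads "We hypothesise that over a 4-month period the intervention will increase physical activity" by about half. The next sentence adds: "We also hypothesise that these effects will be maintained at 12 and 24 months post intervention". The total of 200 then allows for the effect lasting 24 months and for up to 40% dropout.

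**The concern.** The rule gives a reason for leaving every test at 0.05, and the reason is wrong. Stating a hypothesis beforehand protects against choosing it afterwards. It does nothing about the number of chances to be wrong: three pre-stated tests at 0.05 still carry three chances of a false positive. An analysis plan that followed this sentence would carry the error forward.

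The premise also fails within its own paragraph. Regressions meant to find out which baseline characteristics predict change, or predict revascularisation, are searches and not hypotheses fixed in advance, yet the same threshold applies to them.

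At stake is what counts as success on the primary outcome. The 4-month difference, the 24-month difference or an overall group effect could each be presented as the primary result, and the choice could be made after the results are known.

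**Working it through.** **Inputs, all from Sample size calculation.** Means and SDs: "mean daily step counts of 5000 ± 3400 for those receiving the counselling intervention compared to 3300 ± 2200". Error rate and correlation: "alpha 0.05, within-subject between visit correlation 0.6". Size and power: "We require 62 participants per group (power 90" %).

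**Step 1: what was the trial sized for?**
- Difference: 5000 − 3300 = 1700.
- Root-mean-square SD: √[(3400² + 2200²)/2] = √8,200,000 = 2863.6.
- Two-sided test at 0.05, 90% power: n = 2 × (1.960 + 1.282)² × 2863.6² / 1700² ≈ 60 per group. The t-test version gives 61. The plan states 62, so its figure is reproduced closely.
- Using the correlation of 0.6 would give fewer: 60 × (1 − 0.36) = 38.4, so 39, with baseline adjustment; 60 × 2 × (1 − 0.6) = 48 for a change score.
- Dropout: 60/(1 − 0.4) = 100, the planned number per group. Starting from 62 gives 104.

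The stated 62 therefore matches one unadjusted comparison, at one time, at the full 0.05.

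**Step 2: error rate if success at any visit counts.** Take three two-sided tests at 0.05 with no true effect. The quantity is P(max |Z| > 1.96) for three normal statistics with common correlation ρ. With the same participants at each visit and no baseline adjustment, ρ equals the between-visit correlation of 0.6. If baseline is adjusted for and all visits correlate 0.6, the remaining correlation is (0.6 − 0.36)/(1 − 0.36) = 0.375. Simulation with 3,000,000 draws gives:

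| ρ | P(at least one false positive) |
|---|---|
| 0 (upper limit, 1 − 0.95³) | 14.3% |
| 0.375 | 13.2% |
| 0.6 (stated) | 11.8% |
| 0.8 | 9.8% |
| 0.9 | 8.3% |

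All exceed 5%. A single contrast named beforehand, whether one visit or one overall group effect, would hold 5%.

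**Step 3: what would control cost?**
- Three co-equal visits with Bonferroni, 0.05/3 = 0.0167: 77 per group, or 77/0.6 ≈ 129 per group (258 in total) after 40% dropout, against 100 and 200 planned. With 60 to 62 evaluable per group, unadjusted power falls from 90–91% to 80–82%.
- Fixed sequence starting at 4 months: each test stays at 0.05 and n stays as planned. At the design difference, power for the 4-month step is 90.2% with 60 evaluable per group and 98.7% with 100.

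**The case against.** The best reply is that 4 months is already the implied primary time. The powered difference is tied to that period, and an effect said to be maintained later presupposes one at 4 months, so the wording is close to an ordered hypothesis. The article condenses a longer protocol, and the exact contrast could be left to that or to an analysis plan. A mixed model can also yield one overall test.

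Much of this stands. No sentence says that a win at any visit suffices, so the error rates above are conditional and are not the trial's stated error rate. The rule sets a per-test threshold and makes no familywise claim. The lean towards 4 months is not conclusive, however, because the same section sizes recruitment for maintenance over 24 months and one of the article's research questions concerns sustained behaviour change. And the sentence that justifies 0.05 throughout is an affirmative statement, so later detail would have to overturn it.

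Two stronger readings are tempting and are not supported:
- **Two primary measures.** A reader might infer these from the plural in the secondary outcomes section, "In addition to the primary measures of daily physical activity level and walking (steps/day"), and so count six primary tests with an error rate near 19%. The primary outcome section defines the measure as steps per day, the analysis paragraph names one primary outcome, and only step counts are powered. The stated correlation of 0.6 applies between visits, not between different measures.
- **Secondary findings claimed as confirmed.** A reader might infer this from the shared threshold. The article labels these outcomes secondary and already plans effect sizes with 95% confidence intervals. Unadjusted secondary tests are acceptable if they are read as supportive; the gap is only that the rule does not say so.

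**Conclusion.** The concern holds in a limited form. The justification for using 0.05 everywhere is invalid as written. The one primary outcome carries hypotheses at three visits, with 4 months implied as the lead but never named.

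If success at any one visit were claimed, the chance of a false positive on the primary outcome would be about 12% at the article's own correlation, and roughly 10% to 13% for correlations of 0.8 to 0.375. That rests on three separate two-sided tests, equal correlation between visits and no true effect at any of them. With one pre-named contrast the excess disappears. The invalid clause is certain; the inflation depends on how success is declared, which the article leaves open. This should be corrected, and wording is enough to do it.

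**What to change.** - Delete the statement that a priori formulation justifies the 0.05 threshold.
- Name the between-arm difference in activPAL steps/day at 4 months, estimated from the mixed model, as the single primary contrast. It is the time point of the sample-size difference.
- Test 12 months and then 24 months in fixed sequence, each two-sided at 0.05 and only if the previous test succeeds. This holds 5% over the three visits and gives the sustained-change question a defined test.
- State that secondary outcomes and the predictor analyses are supportive, reported as estimates with nominal 95% confidence intervals.

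The cost is protocol or analysis-plan wording, settled before any unblinded analysis; the article reports the trial as ongoing at submission. Alpha and sample size do not change. The small downside is that a later visit cannot be claimed as confirmatory if the 4-month test fails.
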